## Abstract

**Background:**

Sudden cardiac death remains a leading cause of mortality in Canada, resulting in more than 35,000 deaths annually. Most cardiac arrest victims collapse in their own home (85% of the time) and 50% are witnessed by a family member or bystander. Survivors have a quality of life similar to the general population, but the overall survival rate for out-of-hospital cardiac arrest (OHCA) rarely exceeds 8%. Victims are almost four times more likely to survive when receiving bystander CPR, but bystander CPR rates have remained low in Canada over the past decade, not exceeding 15–25% until recently. Telecommunication-assisted CPR instructions have been shown to significantly increase bystander CPR rates, but agonal breathing may be misinterpreted as a sign of life by 9–1-1 callers and telecommunicators, and is responsible for as much as 50% of missed OHCA diagnoses.

We sought to improve the ability and speed with which ambulance telecommunicators can recognize OHCA over the phone, initiate timely CPR instructions, and improve survival.

**Methods:**

In this multi-center national study, we will implement and evaluate an educational program developed for ambulance telecommunicators using a multiple baseline interrupted time-series design. We will compare outcomes 12 months before and after the implementation of a 20-min theory-based educational video addressing barriers to recognition of OHCA while in the presence of agonal breathing. Participating Canadian sites demonstrated prior ability to collect standardized data on OHCA. Data will be collected from eligible 9–1-1 recordings, paramedic documentation and hospital medical records. Eligible cases will include suspected or confirmed OHCA of presumed cardiac origin in patients of any age with attempted resuscitation.

**Discussion:**

The ability of telecommunication-assisted CPR instructions to improve bystander CPR and survival rates for OHCA victims is undeniable. The ability of telecommunicators to recognize OHCA over the phone is unequivocally impeded by relative lack of training on agonal breathing, and reluctance to initiate CPR instructions when in doubt. Our pilot data suggests the potential impact of this project will be to increase absolute OHCA recognition and bystander CPR rates by at least 10%, and absolute out-of-hospital cardiac arrest survival by 5% or more.

**Trial registration:**

Prospectively registered on March 28, 2019 at ClinicalTrials.gov identifier: NCT03894059.

## Background

### Cardiac arrest

Sudden cardiac death remains a leading cause of mortality in Canada, resulting in more than 35,000 deaths annually [1–3]. This means that a cardiac arrest occurs every 12 min [3] and most of those occur in prehospital settings [4]. Most cardiac arrest victims are still active members of society. They collapse in their own home 85% of the time and 50% are witnessed by a family member or bystander [4]. Survivors have a quality of life similar to the general population [5], but the overall survival rate for out-of-hospital cardiac arrest (OHCA) rarely exceeds 8% [4, 6, 7]. Victims are almost four times more likely to survive when receiving bystander CPR, but bystander CPR rates have remained low in Canada over the past decade, not exceeding 15–25% until recently [4, 7].

### Telecommunication-assisted CPR instructions

Telecommunication-assisted CPR instructions, where telecommunicators provide CPR instructions or reminders over the telephone to 9–1-1 callers reporting a victim in cardiac arrest, have been shown to significantly increase bystander CPR rates [8]. However, in the first minutes following cardiac arrest, some victims will take short, labored, noisy, gasping breaths. This abnormal breathing, otherwise known as agonal breathing, may be misinterpreted as a sign of life by 9–1-1 callers and telecommunicators [8–10], and is responsible for as much as 50% of missed OHCA diagnoses [10]. These missed OHCA diagnoses can result in withholding or delaying the delivery of telecommunicator-assisted CPR instructions.

### Prior related work

Over the past 10 years, we have completed a number of unique studies in the field of telecommunication-assisted CPR instructions, leading up to this current project.
**Pilot Evaluation of Telecommunication-Assisted CPR Instructions in Ottawa**

This before-after study took place over an 18-month period before and after the introduction of telecommunicator-assisted CPR instructions in the Communication Centre in Ottawa, Ontario. A total of 529 cases were included and bystander CPR rates increased from 16.7 to 26.4% (95% confidence interval (CI) 8.5–11.3%; p-0.006) [8].
2)**Multi-Centre Evaluation of Effectiveness of Telecommunication-Assisted CPR Instructions**

This study took place in several Ontario Communication Centres. In this before-after interrupted time series study including 6494 cases before and after the introduction of telecommunicator-assisted CPR instructions, bystander CPR rates increased from 14.9 to 28.7% (*p* < 0.0001) and survival increased from 4.1 to 5.2% (adjusted odds ratio 1.28; 95% CI 1.02–1.62; *p* = 0.04). Telecommunicators recognized 65.9% of all OHCA. Agonal breathing (present in 22.7% of all OHCA) accounted for 47.6% of missed diagnoses, resulting in inappropriately withheld bystander CPR for 240 victims [11, 12].
3)**Systematic Reviews of Factors Leading to the Recognition of Cardiac Arrest by Telecommunicators**

These two systematic literature reviews were peer-reviewed by the International Liaison Committee on Resuscitation (ILCOR) and provided the scientific background from which the 2010 and 2015 resuscitation guidelines for telecommunication-assisted CPR instructions were derived [13, 14]. The reviews conclude that telecommunicators should receive specific instructions on how to recognize the presence of agonal breathing in order to improve their recognition of cardiac arrest.
4)**National Survey of Factors Associated with the Successful Recognition of Agonal Breathing**

This National Survey was distributed to telecommunicators from 24 cities in four provinces (*n* = 404). The survey was developed using the constructs of the Theory of Planned Behavior, which elicits salient attitudes, social influences and control beliefs suggesting corresponding educational behavior-change techniques to improve recognition of agonal breathing and cardiac arrest [15, 16].
5)**Before-After Controlled Pilot Study**

In this recently-completed study we demonstrated we could improve absolute bystander CPR rates by 12.9% and survival to hospital discharge by 8.4% in Ottawa after implementing a theory-based (TPB) educational program on agonal breathing for telecommunicators. Agonal breathing was present in as many as 25.6% of cases, but was responsible for only 15.8% of missed cases (compared to almost 50% previously) [7].
6)**National Survey of Canadian Communication Centres**

Finally, most recently, a National Survey of all Canadian Communication Centres was undertaken to obtain information on their organizational structure, dispatch systems in use, education curriculum and performance monitoring. The information obtained indicates that most centres utilize the Medical Priority Dispatch System, require a High School diploma as minimum entry level education and telecommunicators receive no or minimal education in recognizing agonal breathing as a sign of OHCA [17].

### Canadian resuscitation outcomes consortium (CanROC)

The Canadian Resuscitation Outcomes Consortium (CanROC) collects population-based data on out-of-hospital cardiac arrest in a registry that aims to capture 100% of OHCA patients assessed by emergency medical services within each contributing site’s catchment area. This initiative builds on the expertise acquired by the three Canadian sites that contributed to the North American Resuscitation Outcomes Consortium (ROC) between the years of 2006 to 2016 [18]. Standardized information on Canadian cardiac arrest victims were collected from Communication Centre records, fire reports, paramedic documentation, defibrillator files and hospital records by British Columbia, Toronto communities (Rescu) and the Ottawa/OPALS Group (Ottawa, Windsor, London, Niagara, Sudbury, Thunder Bay). New funding has allowed these 3 sites to continue registry data collection while also expanding to include other sites across Canada, in an effort to establish a National Cardiac Arrest Registry. This will allow for unique opportunities to obtain current information on cardiac arrest occurrence and prognosis, to study different models of care and delivery, to collaborate on multi-province initiatives and to engage and mentor new researchers. This study will rely on data collected by CanROC to collaboratively obtain key study outcomes quickly and economically.

### Importance of this research

The ability of telecommunication-assisted CPR instructions to improve bystander CPR and survival rates for OHCA victims is undeniable. It is also unequivocal that the ability of telecommunicators to recognize OHCA over the phone is impeded by their relative lack of training regarding the significance of agonal breathing as a symptom of OHCA, and their reluctance to initiate CPR instructions when in doubt. Agonal breathing is present in approximately 25% of all OHCA victims. It is responsible for as much as 50% of all unrecognized OHCA, the consequence of which is withheld bystander CPR and most often death.

#### Hypothesis

We hypothesize that the educational program will increase absolute OHCA recognition and bystander CPR rates by at least 10%, and absolute OHCA survival by 5% or more.

#### Objectives

The overall aim of this research project is to improve the ability and speed with which ambulance telecommunicators can recognize OHCA over the phone, initiate timely CPR instructions, and improve survival for OHCA. Specific objectives are to:
Measure the impact of telecommunication-assisted CPR instructions on overall survival rates for OHCA following the implementation of an educational program on agonal breathing.Measure the impact of the educational program on overall community bystander CPR rates.Measure the frequency with which telecommunication-assisted CPR instructions are appropriately provided following the educational program.Quantify the frequency and impact of the presence of agonal breathing on OHCA recognition following the implementation of an educational program.Measure if the educational program decreases time delays before OHCA is recognized and telecommunication-assisted CPR instructions are initiated.Measure the impact of the studied community/site on OHCA recognition and OHCA outcomes.Measure the impact of the telecommunication system/platform used on OHCA recognition and OHCA outcomes.Measure the impact of telecommunicators’ training background and current local training on agonal breathing on OHCA recognition and outcomes.Identify high-quality recordings that will be used to derive a cognitive computing (IBM Watson)-assisted algorithm to rapidly recognize the presence of OHCA during conversations between 9 and 1-1 calls and telecommunicators. (Future project objective)

## Methods/design

### Study design

We propose a multiple baseline interrupted time series (ITS) design (using month as a time unit) which compares our stated outcomes over 12 months before and 12 months after the implementation (over a 1-month transition period, with possible inter-site variability based on site size) of the theory-based educational intervention on recognition of agonal breathing. The ITS design is a robust quasi-experimental design which is ideal for our study because: 1) Withholding this potentially life-saving intervention from control groups could possibly be considered unethical by some review boards; 2) Most sites would only participate if ultimately given an opportunity to implement the intervention; and 3) It will account for heterogeneity across sites in their underlying baseline trends and changes in response to the intervention. In addition, this design will give us the ability to explore the effects of our intervention while taking into account possible seasonal variations and secular trends.

Each site will implement the educational program on agonal breathing at their earliest convenience, and enter into a 12-month evaluation period (12 months/time periods after the implementation of the educational program). The evaluation period for all sites could possibly be spread over 18 months given their respective training completion. This will leave us with 6–12 months to complete data collection and analyses.

Data for the 12-month control period preceding the implementation of the educational program (12 months/time periods) will be obtained retrospectively once a site’s evaluation period is determined. Ambulance Communication Centres are already required to keep their telecommunication recordings for at least 5 years, and CanROC will have already prospectively collected all the other required outcome measures throughout.

### Educational intervention

There is a growing body of literature in social sciences supporting the identification of evidence-based competencies required to effectively change behaviour in health care related interventions [19–21]. The Theory of Planned Behaviour (TPB) can be a useful, systematic tool to identify barriers to and facilitators of change, aiding in the design of appropriate forms of intervention [22–28]. The TPB proposes that the strength of an individual’s intention (or motivation) to engage in a behaviour, and the degree of control they feel they have over that behaviour (perceived behavioural control) are the proximal determinants of engaging in that behaviour [29]. The TPB also proposes that intention strength is determined by three variables: attitudes towards the behaviour, subjective norms, and perceived behavioural control. Those theoretically derived determinants of behaviour can be mapped to specific behaviour change techniques [30]. This approach was successful in clinical trials on smoking cessation [21, 31, 32], colorectal cancer screening [33], and physical fitness [34].

The proposed education interventions were developed using behaviour change techniques specifically mapped to address the modifiable factors identified by our national survey of ambulance telecommunicators [15]. These techniques will include:
**Information about the significance of agonal breathing:**This first module will consist of a 20-min video detailing information about the early clinical signs of cardiac arrest, including agonal breathing. The original 30-min video used in our pilot study was reviewed in collaboration with a committee of telecommunication leaders from participating sites. Its content was shortened by 10 min, references to existing protocols were updated, and a visual representation of agonal breathing was added. Telecommunicators employed by the participating sites will all review this short educational video individually. Site implementation will commence once all regulatory requirements are met for that site and is expected to be staggered over a 6-month period for all sites. Completion of staff training at each site is expected to be completed within 1 month.**Modeling/demonstration of desired behavioural skills:**The video will include a number of real interventions involving the description of agonal breathing by 9–1-1 callers. These interactions are judged to be optimal examples to emulate.**Rehearsal of desired skills:**A second, shorter module will be updated with new cases of agonal breathing and interactions with 9–1-1 callers and completed once in the middle of the intervention period.**Monitoring/reinforcement and feedback:**Each time an ambulance telecommunicator is involved with a cardiac arrest call, they will be provided with a report card which will include various time intervals measured during the review of the recording (time to cardiac arrest recognition, time to initiation of chest compressions), whether or not the victim was indeed in cardiac arrest upon EMS arrival at the scene, and an opportunity to review their performance with their supervisor. We understand that not all sites will have the resources in place for any or all of these feedback measures. We will work with each site to determine their capacity.

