### Case identification

A list of potential eligible cases will first be identified by each ambulance Communication Centre for each month of the study period. The calls will be flagged using a combination of procedure and complaint codes for inclusivity. Dispatch platform systems differ between sites, thus, details will be outlined with each Communication Centre to ensure flagging of cases is consistent. The list will be sent to the Study Coordinating Centre in Ottawa for review.

The Coordinating Centre will cross-check each list against the CanROC list of confirmed and eligible cases for that site over the same time period. Cases will be matched using only run number and date and time of call to establish eligibility. The inclusion and exclusion criteria will be applied based on CanROC details to arrive at a monthly list of eligible cases from which data will be extracted.

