Agonal breathing: Can be defined as abnormal breathing, gurgling sound, moaning, or otherwise. Ambulance telecommunicators are required by protocol to inquire about the presence or absence of agonal or abnormal breathing. The standardized-piloted data collection tool will be used to independently document the presence or absence of agonal breathing, as described by the 9–1-1 caller to the telecommunicator. In a previous evaluation of inter-rater reliability for the recognition of agonal breathing, we observed substantial agreement (kappa statistics reported) for the presence of agonal breathing between telecommunicators and investigators, between telecommunicators, and within themselves when asked to repeat the exercise 4 months later [8].Recognition of OHCA by telecommunicators: According to protocols, ambulance telecommunicators assume the presence of cardiac arrest when the 9–1-1 caller describes a victim that is lifeless (unresponsive, not breathing, or not breathing normally).Recordings of the OHCA cases from participating ambulance Communication Centres will be reviewed and reasons why cardiac arrest may not have been recognized by the telecommunicator (including the presence of agonal breathing) will be documented.Determination of cardiac origin of OHCA: We will use the Utstein definition for cardiac arrest of cardiac origin [35]: “If an EMS provider or physician did not witness the cardiac arrest, he/she may be uncertain as to whether a cardiac arrest actually occurred. An arrest is presumed to be of cardiac etiology unless it is known or likely to have been caused by trauma, submersion, drug overdose, asphyxia, exsanguination, or any other non-cardiac cause as best determined by rescuers.”

Cardiac origin of OHCA is usually first suspected/documented by the paramedic crew responding to the scene, and subsequently confirmed using hospital discharge summaries or coroner’s data. This information will be readily available from the CanROC registry.

#### Objective 5

Speed with which OHCA is recognized and telecommunication-assisted CPR instructions are initiated: All 9–1-1 communications are recorded on digital files (for e.g. Canadian Voice Data Switching (CVDS) files) which include a running digital clock. We will record the time at which OHCA was recognized by telecommunicators, the time at which CPR instructions are initiated, and calculate time intervals from the initiation of the 9–1-1 call to these time stamps.

#### Objectives 6, 7, and 8

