**Fig. 1 Fig1:**
[figure not shown]
Proposed data flow options

Each month during the study period, a list of potentially eligible cases will be generated by each participating Communication Centre and sent to the Study Coordinating Centre in Ottawa for classification. The Coordinating Centre will obtain a parallel list of study-eligible, confirmed cardiac arrest cases over the same time period, from the corresponding CanROC Site or the CanROC Registry. The two lists will be compared and classified into one of the four categories (eligible, ineligible, missed, overcalled). This final list of eligible cases will then be sent back to the Communication Centre for preparation. Depending on the resources available at each site, one of the following will then occur:
Study staff at each Communication Centre will locate the 9–1-1 recordings, remove all identifying information and securely transfer them to the Study Coordinating Centre in Ottawa for review. Trained study staff in Ottawa will extract the study data and enter it into the study database.Study Coordinating Centre will train local study staff to review 9–1-1 recordings, extract the study data and enter it into the study database.

The Study Coordinating Centre will adopt a pragmatic approach to accommodate possible manpower limitations, provincial regulations, privacy concerns or other issues. Where there are deviations from these processes, the revised flow will be documented.

Once the recordings have been reviewed and the required information obtained, the Study Coordinating Centre will request the CanROC variables for the eligible and missed cases.

The data will be pushed securely to the study database and will be linked via run number and call date.

Extensive steps have been taken to ensure the protection of patient privacy. At the Study Coordinating Centre, all incoming data will have been transferred securely and stripped of identifying information. No direct identifiers are included in the data being collected, information which is obtained during routine, standard care with no direct contact with research participants. De-identified electronic files will be stored securely on a network folder with access limited to essential study personnel. Paper files are stored in a locked cabinet, in a locked room.

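### Recognition and time-to-recognition are judged from recordings in a workflow that lets the reviewer infer the period, so a coding shift could pass for an intervention effect

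*Protocol article*

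**What the plan says.** All references are to the protocol article.

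- **Educational intervention (monitoring and feedback item).** After a cardiac arrest call, telecommunicators receive a report card that includes "various time intervals measured during the review of the recording (time to cardiac arrest recognition, time to initiation of chest compressions". The text adds a limit: "not all sites will have the resources in place for any or all of these feedback measures".
- **Study design.** Data for the 12-month control period "will be obtained retrospectively once a site’s evaluation period is determined". Centres must keep recordings for at least five years.
- **Case identification; Data management and flow.** Lists are drawn up by month. "Cases will be matched using only run number and date and time of call to establish eligibility". Study data are later linked by run number and call date.
- **Data management and flow.** "Depending on the resources available at each site, one of the following will then occur": either de-identified recordings go to trained staff in Ottawa, or the "Study Coordinating Centre will train local study staff to review 9–1-1 recordings, extract the study data and enter it into the study database". Departures from these processes are to be documented.
- **Method of assessment, Objectives 4 and 5.** Reviewers use a standardized, piloted tool to record whether the caller described agonal breathing. They also note when recognition occurred and when instructions began, and "reasons why cardiac arrest may not have been recognized by the telecommunicator (including the presence of agonal breathing) will be documented".
- **Data analysis.** Recognition rates and time intervals are compared before and after with the methods of Objectives 1 and 2, or similar ones. Objective 3 and the frequency of agonal breathing are reported descriptively.

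**The concern.** The running clock on a recording supplies the time, but a listener decides at which moment, if any, the telecommunicator recognised the arrest. If that decision is made differently for calls known or guessed to come after training, the measured rate or interval changes although the calls have not.

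An interrupted time series does not protect against this. It adjusts for trend, but a coding change that begins at implementation enters the model as a level change. Staggering the sites does not remove it either, if the shift follows each site's own start date.

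At stake is the recognition hypothesis (a gain of at least 10 points) and, with it, the explanation of how the training would improve survival.

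**Working it through.** **1. Can the period be inferred?** Set the statements side by side:

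- Report cards are part of the intervention, so a review that yields one is a review of an after-period call.
- Baseline recordings are pulled retrospectively and can form a separate set.
- Call date is used for monthly listing and for linkage.
- Removing identifying information is presented as a privacy step. The article does not say that it removes the date.
- Nothing ties a site to one review route, or to one set of reviewers, across both periods.

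The article does not state what the coder sees. The conclusion is that the workflow allows the period to be inferred, not that the period is known.

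**2. Which outcomes are exposed?** Recognition rate and the Objective 5 intervals are exposed, because they are both coded from recordings and compared by time series. Survival comes from hospital or coroner records, and bystander CPR from the first responder's patient care record; neither is exposed.

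**3. How large a shift would matter? (illustration)**

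Inputs from the article:

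- Recognition 65.9% in the earlier multi-centre Ontario study (Prior related work), taken here as the baseline.
- 6000–7000 cases per year and 500 per month (Sample size).
- Table 1 total of 8312 cases per year.

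Assumptions: two-sided 5%, independent binomial errors, all regions treated as one series, 12 months before, 1 censored, 12 after.

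The plan's own figure: 6000/12 = 500, which reproduces. It is the low end of the stated range, since 7000/12 = 583.

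- Missed calls: 1 − 0.659 = 34.1%. A 10-point gain equals 0.10/0.341 = 29% of them.
- Variance of a monthly rate: 0.659 × 0.341/500 = 0.000449.
- Level change at the first post-implementation month (month 14) is the fitted post line minus the extrapolated pre line. Twelve consecutive months have a sum of squares of 143, so the variance factor is (1/12 + 5.5²/143) + (1/12 + 7.5²/143) = 0.295 + 0.477 = 0.772.
- SE = √(0.000449 × 0.772) = 1.86 points. 1.96 × SE is about 3.6 points, or 0.036/0.341 = about 11% of missed calls.
- With 583 or 693 (8312/12) cases per month, the threshold is 3.4 or 3.1 points.
- Simple comparison of 6000 with 6000, as a reference: 1.96 × √(2 × 0.659 × 0.341/6000) = 1.7 points, or 5% of missed calls.
- Contrast with the projected rate at the twelfth post-implementation month: SE 3.53 points, so 1.96 × SE = 6.9 points. This measure is less sensitive to a constant shift.

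Positive autocorrelation or extra variation between regions would raise these thresholds.

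**The case against.** The strongest reply is that much of this is inference. No sentence says that coders know the period. An article condenses the full protocol, which may contain a masking step, so silence on masking is not in itself a fault. That stands, and the point rests on the workflow as described.

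Several stronger readings are tempting but not supported:

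- *That reviewers definitely know the period.* The article does not say what they see.
- *That local reviewers work for the centre under evaluation and know the training content.* The text says only that they are local study staff trained by the Coordinating Centre.
- *That reviewer drift is fully aligned with before and after.* Drift follows the date of coding. Baseline calls could be coded during the evaluation period, and with staggered sites an Ottawa reviewer may be coding both periods at once.
- *That report cards create the problem everywhere.* They depend on site capacity. The article also does not say outright that the review behind them is the outcome extraction, although time to recognition appears in both.
- *That all of Objectives 3 to 5 is affected in the same way.* The level-change argument does not reach the parts reported descriptively.

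There are real safeguards: a standardized piloted tool, trained staff, independent documentation of agonal breathing, a protocol-based notion of recognition, clock time stamps and kappa statistics. They reduce random error. They do not rule out coding that differs by period, and the earlier agreement study cited concerned agonal breathing, not agreement by period.

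**Conclusion.** The concern holds in a limited form. For recognition rate and for times to recognition and to instructions, the described workflow lets the reviewer infer the period and allows the review route to differ between a site's two periods. A resulting coding shift could not be told apart from a level change.

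Under the stated assumptions, a shift of about 3.6 points (3.1 to 3.6 over the article's case volumes) would reach nominal significance for the level change. That is roughly a third of the hypothesised 10-point gain. The documents give no basis for how often coding would shift, or in which direction, so these figures show sensitivity and are no evidence that bias will occur.

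The primary outcome and bystander CPR are untouched. The point is worth acting on because the remedy is cheap.

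**What to change.** 1. Give each recording a study number, and hide call date and period from the coder.
2. Code each site's after-period batches mixed in random order with its baseline recordings. These already exist by then, so coding need not wait for the end of the evaluation period.
3. Keep one review route and the same reviewers for both periods of a site.
4. Have a coordinator who holds the linkage key, not the coder, produce any report cards from the coded intervals. The feedback itself is unchanged and needs no extra listening at sites.
5. Optionally, have existing Ottawa reviewers recode a small date-hidden sample from locally coded sites and report agreement by period.

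If the full protocol already masks coders and fixes the route, a sentence saying so is enough.

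**Cost:** a linkage key to maintain, because data are now linked by run number and call date; possibly some file processing, if the running clock shows the calendar date; slightly later coding of some calls; and, if step 5 is adopted, a small sample coded twice.
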